### 22.1 GLMs

| #  | Variable Type                 | Distribution                              | Link Fn   | Example Stata Code †††                      |
|----|-------------------------------|-------------------------------------------|-----------|--------------------------------------------------------|
| 1  | Continuous (Normal)           | Gaussian                                  | Identity  | glm depvar indepvars, family(gaussian) link(identity)  |
| 2  | Continuous (SPC) † | Inverse Gaussian                          | Power -2  | glm depvar indepvars, family(igaussian) link(power -2) |
| 3  | Binary                        | Binomial (multiple) or Bernoulli (single) | Logit     | glm depvar indepvars, family(binomial) link(logit)     |
| 4  | Count/Rate (Poisson)          | Poisson                                   | Log       | glm depvar indepvars, family(poisson) link(log)        |
| 5  | Count/Rate (NB)               | Negative binomial                         | Log       | glm depvar indepvars, family(nbinomial) link(log)      |
| 6  | Continuous (SPC) † | Gamma                                     | Power -1  | glm depvar indepvars, family(gamma) link(power -1)     |
| 6  | Continuous (Time)             | Gamma?                                    | Power -1? | glm depvar indepvars, family(gamma) link(power -1)     |
| 99 | Time-to-event                 | Exponential ††                 | Log       | glm depvar indepvars, family(exponential) link(log)    |

† SPC = Skewed positive continuous variable.

†† Not available in Stata. Code shown is synthetic. GLMs in this case would require another language

††† For a full list of families, link functions in Stata and their valid combinations, please see Stata help. Note that “inverse” is the same as “power -1”, “inverse squared” is the same as “power -2”, and so on

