## 2. OVERVIEW

The secondary outcomes will be summarised descriptively by trial group. If appropriate, the effect size and 95% confidence intervals will be estimated with regression models. Both absolute and relative effect sizes will be reported.

Complications will be summarised using one or more of the following:

- count/percentage of participants with any complication
- count/percentage of participants with any complication by grade
- count/percentage of participants with the highest grade of complication reported
- count/percentage of participants with any type of complication
- count of total complications.

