|                                        | v. Recurrence                                                 | v-vi: 3 years                                                        | N/A: not model                  |               |            |
|                                        | vi. New primary/ secondary cancer                             | ditto                                                                | N/A: not model                  |               |            |
| 4. Operative outcomes                  | vii. Intraoperative blood loss                                |                                                                      |                                 |               |            |
|                                        | Count/rate (transfused Y/N)                                   | vii-ix: Discharge                                                    | Binary                          | Binomial      |            |
|                                        | units transfused (including untransfused)                     | ditto                                                                | Continuous                      | See lookup    |            |
|                                        | viii. Operative time                                          | ditto                                                                | Continuous                      | See lookup    |            |
|                                        | ix. Conversion to open surgery                                | ditto                                                                | Binary                          | Binomial      |            |
|                                        | x. Surgical site infection                                    | x-xiii: Discharge and 30-days post-op                                | Binary                          | Binomial      |            |
|                                        | xi. Stoma rates                                               | ditto                                                                | Binary                          | Binomial      |            |
|                                        | xi. Stoma complications                                       | ditto                                                                | Binary                          | Binomial      |            |

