|                                        | xii. Radiologically -defined anastomotic leaks                | ditto                                                                | Binary                          | Binomial      |            |
|                                        | xiii. Length of time in intensive care unit                   | ditto                                                                | Continuous                      | See lookup    |            |
|                                        | xiii. Length of time in high dependency unit                  | ditto                                                                | Continuous                      | See lookup    |            |
|                                        | xiv. Re-operation rates                                       | xiv-xv: 30-days post-op and 3 years                                  | N/A: not model                  |               |            |
|                                        | xv. Re-admission rates                                        | ditto                                                                | N/A: not model                  |               |            |
|                                        | 5. Hospital stay                                              | xvi. Length of hospital stay (fitness to discharge)                  | xvi: Discharge                  | Time-to-event | See lookup |
|                                        |                                                               | xvii. Days alive and out of hospital                                 | xvii: 30-days post- operatively | Time-to-event | See lookup |
| 6. Anthropometry                       | xviii. Weight                                                 | xviii-xix: Baseline, pre-operative assessment 4, and 30 days post-op | Continuous                      | See lookup    |            |
|                                        | xix. Fat-free mass (absolute kg)                              | ditto                                                                | Continuous                      | See lookup    |            |
|                                        | xix. Fat-free mass (relative %)                               | ditto                                                                | Continuous                      | See lookup    |            |

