### 8.1 vii. Intraoperative blood loss

This outcome is reported using two variables: by the presence of intraoperative blood transfusion and by the number of units transfused (including the untransfused). The information to calculate it is derived from the fact of an intraoperative blood transfusion and the number of blood units used. These variables are recorded on the CRF Hospital Stay and Discharge.

The first variable is a binary variable and collectively a count/rate (0-n/%). The second variables are continuous variables and measurements of amount.

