#### 8.7 xiii. Time in intensive care unit and time in high dependency unit

The information to calculate these two lengths of time is derived from the ward and time details on the CRF Hospital Stay and Discharge. Each one is a continuous variable and a measurement of time.

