## 22.4 Green, JA (2021)

The paper Green, JA (2021) (see[5] for more details) also gave a guide for which variable types would need which families. This guide can be used in tandem with the tables above

| Variable Type                     | Family                          |
|-----------------------------------|---------------------------------|
| Count variables                   | Poisson                         |
| Count variables                   | Negative Binomial               |
| Count variables with excess zeros | Zero-Inflated Poisson           |
| Count variables with excess zeros | Zero-Inflated Negative Binomial |
| Count variables with excess zeros | Hurdle Models                   |
| Overdispersed count variables     | Quasi-Poisson                   |
| Overdispersed count variables     | Quasi-Negative Binomial         |
| Overdispersed count variables     | Quasi-Binomial                  |
| Continuous skewed variables       | Gamma                           |

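### The lookup's inverse links for skewed and time outcomes do not yield the promised effect measures, and ICU/HDU time has no suitable model that admits zeros

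*Combined protocol and SAP*

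**What the plan says.** All of this is in the supplement on secondary outcomes that accompanies the SAP.

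- **Typing.** The outcome table in Section 5 types "xiii. Length of time in intensive care unit", the matching HDU item, operative time, sit-to-stand time and units transfused as continuous, and refers the distribution to the lookup. Section 8.7 says of ICU and HDU time: "Each one is a continuous variable and a measurement of time". Section 8.1 reports blood loss partly "by the number of units transfused (including the untransfused"), so untransfused patients enter as zero.
- **Lookup.** Section 22.1 has a Gaussian/identity row for normal outcomes. Skewed positive continuous outcomes get two rows: gamma, coded "glm depvar indepvars, family(gamma) link(power -1"), and inverse Gaussian, coded "glm depvar indepvars, family(igaussian) link(power -2"). The row for continuous time repeats the gamma code, with question marks against both distribution and link.
- **Effect.** Section 2 states: "Both absolute and relative effect sizes will be reported". Section 4.1 defines the treatment effect as the treatment-group term or, where the model has an interaction, the interaction term.
- **Alternatives listed.** Section 22.2 (non-GLMs) has one continuous row, for normal data. Section 22.4 offers zero-inflated and hurdle models for "Count variables with excess zeros" and sends skewed continuous variables to gamma again. Section 25 lists both the inverse and the log as typical links for gamma.

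**The concern.** There are two separate difficulties.

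The first is the scale of the effect. A coefficient on an inverse link is neither a difference nor a ratio of means, and a positive value means a smaller mean. Its clinical meaning changes with the level of the control mean. Someone planning the definitive trial could not use it without a further step, and the supplement does not describe one.

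The second is zeros. A patient who never enters ICU or HDU has zero time there, and the untransfused are kept in deliberately. Gamma and inverse-Gaussian models are for strictly positive data, as the lookup's own label for those rows says. Units transfused is a whole number and could use the count rows if it were typed as a count. ICU and HDU time have no such way out in the listed tables.

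At stake is whether these secondary outcomes are reported in a form that can be read, by a method settled before database lock.

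**Working it through.** The plan states no figure on this point, so there is none to reproduce. The checks concern the form of the models.

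**1. What the treatment term means.** Write m0 for the control mean, m1 for the intervention mean and b for the treatment term.

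- Power -1: b = 1/m1 - 1/m0.
- Power -2: b = 1/m1² - 1/m0².
- Log: b = ln(m1/m0), so exp(b) is the ratio of means.

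Take operative time with m0 = 200 and m1 = 180 minutes (illustrative values, not from the documents):

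- Power -1: 1/180 - 1/200 = 0.005556 - 0.005000 = +0.00056.
- Power -2: 1/32,400 - 1/40,000 = 0.00003086 - 0.00002500 = +0.0000059.
- Log: ln(0.90) = -0.105, so the ratio is 0.90. The difference in means is -20 minutes.

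Now fix b = 0.25 and vary the control mean. Under power -1, m1 = 1/(1/m0 + 0.25). Under power -2, m1 = 1/√(1/m0² + 0.25).

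| Control mean | Power -1: difference, ratio | Power -2: difference, ratio |
|---|---|---|
| 1 | -0.20, 0.80 | -0.11, 0.89 |
| 4 | -2.0, 0.50 | -2.2, 0.45 |
| 8 | -5.3, 0.33 | -6.1, 0.24 |

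One coefficient therefore corresponds to very different differences and ratios.

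**2. Likelihood at zero.** The inverse-Gaussian log-density at 0 is minus infinity. The gamma log-density at 0 is minus infinity for shape 2, plus infinity for shape 0.5, and finite only at shape 1. R, which Section 22 accepts as an alternative to Stata, refused both fits on data containing zeros.

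**3. How many zeros.** The documents give no share of patients with any ICU or HDU time or any transfusion, so 5% to 30% is assumed. With p the non-zero share, expected zeros are 72 × (1 - p). The chance that at least one arm of 36 is all zero, so that 1/mean is undefined, is 1 - [1 - (1 - p)^36]². At p = 5%, 0.95^36 = 0.158, and 1 - 0.842² = 0.29.

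| Assumed non-zero share | Expected zeros of 72 | Chance an arm is all zero |
|---|---|---|
| 5% | 68 | 29% |
| 10% | 65 | 4.5% |
| 20% | 58 | under 0.1% |
| 30% | 50 | under 0.1% |

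**4. Forcing the fit.** Some software will still run a quasi-likelihood version. In 500 simulated trials per scenario (36 per arm, four strata, no treatment effect), the gamma/inverse fit ended in an error, a non-positive linear predictor or non-convergence in 258 (52%), 100 (20%) and 40 (8%) trials at 10%, 20% and 30% non-zero.

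**The case against.** The strongest reply is that the lookup is a guide and not a commitment. The time row carries question marks, variables will be graphed first (Section 22), GLMs are used where possible (Section 4.3), and Section 4.2 lets the team decline to model an outcome, with very low counts as its example. This stands: the plan permits these models without fixing them. It does not dispose of the point. A skewed graph leads back to the same rows, no rule says when ICU or HDU time would go unmodelled, and the choice falls to a statistician who is not blinded (SAP 3.2).

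Some further inferences are tempting, but the documents do not support them:

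- *All time outcomes are affected.* Length of stay and days alive and out of hospital are typed time-to-event (Sections 9.1 and 9.2) and go to other models.
- *Operative time will be reported as 0.00056.* If operative or sit-to-stand time looks roughly normal, the Gaussian/identity row applies and gives a mean difference directly.
- *The promised effects cannot be obtained.* Both can be derived from fitted means. The step is unstated, not impossible. Section 24 also says that not every variable will be shown both ways.
- *Patients with zero would be silently dropped.* Nothing says so. Section 8.1 keeps the untransfused in, and the software outcome found was refusal or instability, not silent exclusion.

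It is also fair that transfusion yes/no is already a separate binary outcome, and that medians with interquartile ranges are already allowed.

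**Conclusion.** The point holds as a minor correction. For skewed positive outcomes Section 22.1 offers only inverse-type links, and the term that Section 4.1 calls the treatment effect is then not on the scale promised in Section 2. Section 25 already lists the log link for gamma, so the two appendices need reconciling. ICU and HDU time have no suitable zero-capable model in the lookup, and units transfused is kept from one only by being typed continuous.

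The algebra in step 1 needs no assumption beyond the illustrative means. The counts and failure rates in steps 3 and 4 depend on the assumed non-zero shares and, for step 4, on the software and fitting method. They show that instability is plausible with 36 per arm and do not predict this trial. That zeros will occur is close to certain, but their number is unknown.

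The consequence is limited. These are secondary outcomes in a feasibility trial without p-values and with intervals regarded as descriptive (SAP 4.1). No progression criterion uses these models.

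**What to change.** 1. **Section 22.1.** Use gamma with a log link in place of the gamma power -1 rows (skewed and time) and the inverse-Gaussian power -2 row. Report the exponentiated treatment term as a ratio of means, and obtain the absolute effect as the marginal mean difference from the fitted means. This serves strictly positive skewed outcomes, such as operative time if its graph is not roughly normal. Keep the Gaussian/identity row.
2. **Sections 5 and 8.1.** Retype units transfused as a count, so that the Poisson, negative binomial or zero-inflated rows apply. Keep the planned transfused yes/no outcome.
3. **Sections 5 and 8.7.** For ICU and HDU time, report the proportion with any stay, the median with interquartile range, and an all-patient mean difference with a 95% confidence interval labelled descriptive. Fit no gamma or inverse-Gaussian model. State whether the mean difference is adjusted for the stratification variables, and note that the interval will be fragile if few patients have any stay.

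The cost is a change to three lookup rows and a few lines on outcome type, made before database lock. No new data are needed, and the same software fits the models.

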**22. APPENDIX B: SCHEDULE OF STUDY PROCEDURES**

| Procedures                        | Assessments                           |                                      |                             |                                                                                       |                              |           |                               |                        |                     |  |
|-----------------------------------|---------------------------------------|--------------------------------------|-----------------------------|---------------------------------------------------------------------------------------|------------------------------|-----------|-------------------------------|------------------------|---------------------|--|
|                                   | From suspicion of cancer to diagnosis | From diagnosis to 3 d post diagnosis | 0-4 days post randomisation | Halfway from starting intervention to surgery (± 3 d)                                 | 4 d pre-op to day of surgery | Admission | Discharge (~5-7 days post-op) | 30 d post-op (27-37 d) | 3y (± 6m) post-op   |  |
|                                   | Pre-screening                         | Screening / baseline                 | Pre-op 1                    | Pre-op 2                                                                              | Pre-op 3                     | Pre-op 4  | Discharge                     | Post-op                | Long-term follow-up |  |
| Informed consent                  |                                       | X                                    |                             |                                                                                       |                              |           |                               |                        |                     |  |
| Eligibility assessment            | X                                     | X                                    |                             |                                                                                       |                              |           |                               |                        |                     |  |

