### 3.3 Sample Size, hypothesis testing, and progression decision

*See also the protocol section "Sample Size Determination"*

With 72 patients (n=36 per arm), the trial will be 90% powered at one-sided 5% level based on the normal approximation approach to detect whether the proportions for the engagement, adherence, and retention criteria in the table 1 are truly above the upper limit of the red zone (>50% engagement, >35% adherence, >65% follow-up) based on an alternative being in the green zone. The collective power for the three criteria of engagement, adherence, and retention is 85% ( $93\% \times 92\% \times 99\%$ ) at 5% level to detect "GO" signals, without multiple testing adjustment. Recalculating the sample size on a binomial approach (sensitivity analysis) provided almost identical estimates.

We are testing against the upper limit of the red zone when the lower limit of the green zone is hypothesised to be true, therefore:

- Null hypothesis: True feasibility outcome is not greater than the upper limit of the red zone.
- Alternative hypothesis: True feasibility outcome is greater than the upper limit of the red zone.

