#### 4.3 Model selection for a given outcome variable

*See Appendix “Use Of The Word “Linear” In Linear Models” for an explanation of the use of the word “linear” even if the underlying curve is a higher polynomial*

The output variables may be continuous or categorical and the input variables may be categorical or continuous. This would imply a logistic model (logistic regression or discriminant analysis) or a linear model (linear regression or ANOVA or ANCOVA or mixed) or a generalized model (GLM) approach. As GLMs are the most capable, we will use GLMs for our models where possible.

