### 9.1 xvi. Length of hospital stay (fitness to discharge)

We will calculate the numbers of days of hospital stay using the date of admission and the date of discharge. The information to calculate it is derived from the admission and discharge data on the CRFs Admission and Hospital Stay and Discharge. It is a time-to-event variable and a measurement of time. Instructions for modelling time-to-event variables are given in the appendices.

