### 22.3 Time-to-event models

| Variable Type | Details                                        | Example Stata Code                                                                                         |
|---------------|------------------------------------------------|------------------------------------------------------------------------------------------------------------|
| Time-to-event | Cox Proportional Hazards Model                 | stset depvar failure(eventvar==1) †
stcox indepvars                                          |
| Time-to-event | Parametric survival models, named distribution | stset depvar failure(eventvar==1) †
streg indepvars, distribution(named distn) †† |

† depvar would be the time-to-event variable, eventvar=0 if censored, 1 if not

†† named distributions currently supported by Stata are exponential, Weibull, Gompertz, lognormal, loglogistic, and ggmma (short for generalized gamma). “Streg” can handle frailty and accelerated-failure-time models as well as proportional hazards models. See Stata help on “streg” for details

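### Length of stay is a whole-day count, but the supplement leaves its model, dispersion assumption and ties method open; some permitted choices give a wrong interval width or a hazard ratio pulled towards 1

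*Combined protocol and SAP*

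**What the plan says.** All references are to the SAP's secondary-outcomes supplement unless stated.

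- **Unit.** Section 9.1: "We will calculate the numbers of days of hospital stay using the date of admission and the date of discharge". The result is a whole number of days. The section types the outcome as time-to-event and refers to the appendices for the model. Section 4.2 lists hospital stay among the outcomes to be modelled.
- **Typical value.** The only indication is a column label in the schedule of procedures (protocol Appendix B): "Discharge (~5-7 days post-op"). No SD, CV or distribution is given.
- **Order of preference.** Section 4.3: "As GLMs are the most capable, we will use GLMs for our models where possible".
- **GLM row.** In section 22.1 the single time-to-event row, numbered 99, reads "glm depvar indepvars, family(exponential) link(log"). Its footnote says that the code is synthetic, is not available in Stata and would need another language.
- **Other options.** Section 22.3 gives "stcox indepvars" with no ties option, and a parametric survival command with a distribution to be named. The list for the latter includes the exponential and also Weibull, Gompertz, lognormal, loglogistic and generalised gamma.
- **Safeguards.** Section 22 says the variable will be graphed, and the heading of 22.2 provides for cases where a GLM cannot cope or is inferior.

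**The concern.** Nothing in the supplement says which of these options applies to length of stay, and they do not perform equally well on this kind of data.

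An exponential model assumes a constant chance of discharge from day 0, which makes the SD equal to the mean. Stays that cluster around a typical discharge day do not behave like that, so the interval would have the wrong width.

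Cox regression assumes in principle that no two patients leave at the same time. Whole-day stays are heavily tied. The Breslow approximation then pulls the hazard ratio towards 1, while the Efron approximation largely does not. Because no method is named and Stata, SAS and R are all acceptable under section 22, the reported effect could depend on the package. Since no p-values are reported, the estimate and its interval are all the reader will have for this outcome.

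**Working it through.** **The plan's own figures.** The documents state no figure for length of stay. Their one power calculation concerns the progression criteria and supplies the sample size used below: "With 72 patients (n=36 per arm), the trial will be 90% powered at one-sided 5% level based on the normal approximation approach". With the one-sample normal approximation, nulls of 0.50, 0.35 and 0.65, alternatives of 0.75, 0.60 and 0.85, and n = 36, 36 and 72, I get 94.1%, 92.8% and 99.5%. The product is 86.9%, against the SAP's 85% (93% × 92% × 99%). That is within 2 points and is not in dispute.

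**Inputs.** 36 per arm and whole days, from the documents. Centre of about 6 days, suggested by the schedule label. The spread, the distribution shape and the effect sizes are assumptions, shown as ranges. No censoring and no covariates.

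**Exponential route, dispersion fixed at 1.**

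- Model SE of the log ratio of means = √(1/36 + 1/36) = 0.236, whatever the data show. The 95% interval is therefore always the ratio multiplied and divided by exp(1.96 × 0.236) = 1.59.
- Actual SE ≈ CV × √(2/36).
- Width relative to the correct width = 1/CV.

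| Assumed CV | 1/CV | Simulated ratio |
|---|---|---|
| 0.25 | 4.0 | 3.9 |
| 0.38 | 2.6 | 2.55 |
| 0.5 | 2.0 | not run |
| 0.6 | 1.7 | 1.6 to 1.7 |
| 0.75 | 1.3 | not run |
| 1.0 | 1.0 | 1.05 |
| 1.2 | 0.83 | 0.89 |

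The first row is what would follow if 5 to 7 days were an interquartile range: SD ≈ 2/1.349 = 1.48, and 1.48/6 ≈ 0.25. The interval is too wide for CV below 1 and too narrow above it.

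**Cox route.** Simulated Weibull stays with mean 6 days and true hazard ratio 1.5, rounded to whole days, 600 trials per row. The last two columns are the mean log hazard ratio as a fraction of the value from unrounded times.

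| CV | Distinct values | HR, unrounded | HR, Breslow | HR, Efron | Breslow fraction | Efron fraction |
|---|---|---|---|---|---|---|
| 0.25 | 7.7 | 1.51 | 1.35 | 1.47 | 0.73 | 0.93 |
| 0.38 | 10.4 | 1.51 | 1.40 | 1.49 | 0.82 | 0.97 |
| 0.6 | 13.3 | 1.51 | 1.44 | 1.50 | 0.89 | 0.99 |
| 0.8 | 14.9 | 1.52 | 1.46 | 1.52 | 0.90 | 0.99 |
| 1.0 | 15.9 | 1.50 | 1.43 | 1.49 | 0.88 | 0.99 |

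A second set assumed a median of 6 days and lognormal stays with log-SD 0.4 to 0.8, rounded up. It gave about 11 to 18 distinct values. A true hazard ratio of 1.5 was estimated as about 1.40 to 1.45 with Breslow and 1.49 to 1.51 with Efron. A true 2.0 became about 1.75 to 1.93 with Breslow and 1.99 to 2.02 with Efron.

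**Shift relative to the noise.** With every patient discharged, SE(log HR) ≈ √(4/72) = 0.236.

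- True 1.5 reported as 1.40 to 1.45: (ln 1.5 − ln 1.40)/0.236 = 0.29 down to (ln 1.5 − ln 1.45)/0.236 = 0.14 standard errors.
- True 2.0 reported as 1.75 to 1.93: 0.57 down to 0.15 standard errors.

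**The case against.** The strongest reply is that nothing in the plan prescribes the faulty analysis.

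- **The lookup does not offer only an exponential GLM or Cox.** A reader might infer this from the GLM row and the Cox row. Section 22.3 also lists free-shape parametric models, which avoid both problems. This stands.
- **Row 99 is weak as an instruction.** It is footnoted as synthetic and unavailable in Stata, the code columns are headed as examples, the variable is to be graphed first, and an inferior GLM may be abandoned. A plot of clustered stays would argue against the exponential. This stands, and makes the exponential error possible rather than expected.
- **The width error needs dispersion held at 1.** In base R the quoted family name is not accepted. The nearest GLM, gamma with log link, estimates dispersion by default, and in one simulated dataset (36 per arm, log-SD 0.4) its SE was 0.084, becoming 0.236 only when dispersion was forced to 1. This stands. The error still arises if an exponential distribution is imposed, including through the parametric survival command.
- **Software always applies some ties method.** So the gap is that none is named, and attenuation follows only under Breslow. The documents state no default, and the argument needs none: the two methods differ and the choice is open.
- **Intervals are nominal and descriptive.** True, and it limits the weight of the point, but it does not make a wrong width informative.

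What the reply does not answer is that no rule selects a sound option. Choosing after the data are graphed leaves the choice until outcomes are visible.

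**Conclusion.** The point holds as a minor one. The supplement does not commit to a length-of-stay model, and the permitted options include an exponential model, whose interval would be wrong by about 1/CV if dispersion is fixed at 1, and a Cox model whose ties method is unstated. Under Breslow ties the log hazard ratio shrinks by roughly 10% to 18% for CVs of 0.38 to 0.8, and by 27% at CV 0.25. Under Efron the loss is about 3% or less from CV 0.38 upwards and 7% at CV 0.25.

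Two stronger conclusions are not supported. One is that the interval will be 2.6 times too wide: that figure needs an assumed CV of 0.38 and fixed dispersion, is not a maximum, and the error reverses when CV exceeds 1. The schedule label for discharge gives no spread, and it counts from surgery while stay counts from admission. The other is that the hazard ratio will be biased: that depends on which ties method is run.

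The consequence is limited. The shift under Breslow is a fraction of one standard error, the hazard ratios of 1.5 and 2.0 are illustrative because the plan sets no target for this outcome, and length of stay is a secondary outcome outside the progression rule.

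**What to change.** In section 9.1 or 22.3, name one length-of-stay model before database lock, with its ties method or its dispersion or shape assumption. A ready choice is Cox with Efron ties: `stcox indepvars, efron`, or ties=efron in SAS or R. Remove row 99 from section 22.1, and exclude the exponential distribution from the parametric survival option, for this outcome.

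If a GLM or parametric model is preferred, that is equally acceptable provided that dispersion is estimated or the shape is free. One example is gamma with log link and estimated scale.

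Row 99 is also the only GLM row for days alive and out of hospital, the other outcome typed as time-to-event, so state that outcome's model at the same time.

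Cost: one code option and one table row. No new data and no change to the sample size.
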